### Study eligibility

#### Inclusion and exclusion criteria

Patients are screened for the following four required conditions: high BP; CKD; overt proteinuria (or macroalbuminuria); and type 2 diabetes mellitus. The detailed inclusion criteria are described in Table 1. The exclusion criteria are described in Table 2. Finally, after learning about the study, patients voluntarily provided written consent to participate.

**Table 1 Tab1:** Inclusion criteria

Age: 19–70 years
Screening visit (Visit 1)
Hypertension in treatment-naïve patients
140 mmHg ≤ SBP < 180 mmHg and DBP < 110 mmHg
Hypertension with treatment, including ACEI/ARB
130 mmHg ≤ SBP < 180 mmHg and DBP < 110 mmHg
eGFR ≥ 30 mL/min/1.73 m^2^ (by MDRD) within the past six months
Urine protein (within the past six months)
ACR ≥ 300 mg/g (or mg/day)
or protein–creatinine ratio ≥ 500 mg/g (or mg/day)
Type 2 diabetes mellitus (diagnosed > 3 months prior) on medications with
no changes in medication regimen/dose within the last three months
Baseline visit (Visit 3)
Hypertension
140 mmHg ≤ SBP < 180 mmHg and DBP < 110 mmHg
eGFR ≥ 30 mL/min/1.73 m^2^ (by MDRD)
Urine protein: ACR ≥ 300 mg/g in spot urine
Type 2 diabetes without regimen change during placebo run-in period

*SBP* systolic blood pressure, *DBP* diastolic blood pressure, *ACEI* angiotensin converting enzyme inhibitor, *ARB* angiotensin receptor blocker, *ACR* albumin–creatinine ratio, *eGFR* estimated glomerular filtration rate, *MDRD* Modification of Diet in Renal Disease

**Table 2 Tab2:** Exclusion criteria

Secondary or malignant hypertension
Inter-arm BP difference: SBP > 20 mmHg or DBP > 10 mmHg
Symptomatic orthostatic hypotension
Cardiovascular history
MI, congestive heart failure (NYHA class III or IV), CABG, PTCA, or angina < 3 months before enrollment
Severe cerebrovascular disease (stroke, cerebral infarction, or cerebral hemorrhage)
Arrhythmia (significant ventricular tachycardia, atrial fibrillation, or atrial flutter)
Significant valvular disease: aortic stenosis or mitral stenosis
Hypertrophic cardiomyopathy
Type 1 DM or HbA1c > 9% at screening
Significant renal or hepatic disease
Dialysis, cirrhosis, biliary tract obstruction, cholestasis, or liver failure
eGFR (MDRD) < 30 mL/min/1.73 m2, hyperkalemia (>5.5 mmol/L) or hypokalemia (<3.5 mmol/L)
AST or ALT > 3 times the upper limit of normal

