### Other secondary endpoints

The other secondary endpoints are summarized as follows: (1) the rate of change in proteinuria in the fimasartan and losartan groups from baseline to weeks 4, 8, and 12; (2) the change in proteinuria in the fimasartan and losartan groups from baseline to weeks 4, 8, and 12; (3) the rate and amount of change in eGFR in the fimasartan and losartan groups from baseline to weeks 4, 8, 12, and 24; (4) the proportion of individuals who developed microalbuminuria (urine ACR < 300 mg/g) in the fimasartan and losartan groups at weeks 4, 8, 12, and 24; (5) the proportion of individuals with ≥ 30% decrease in albuminuria in the fimasartan and losartan groups from baseline to weeks 4, 8, 12, and 24; (6) the proportion of participants with ≥ 50% decrease in eGFR in the fimasartan and losartan groups from baseline to weeks 4, 8, 12, and 24: (7) the rate and amount of change in albuminuria from baseline to weeks 4, 8, 12, 24, 36, 48, 72, 96, 120, and 144 in accordance with the BP control criteria; (8) the rate and amount of change in eGFR from baseline to weeks 4, 8, 12, 24, 36, 48, 72, 96, 120, and 144 in accordance with the BP control criteria; (9) the proportion of individuals with a change in microalbuminuria (urine ACR < 300 mg/g) at weeks 4, 8, 12, 24, 36, 48, 72, 96, 120, and 144 in accordance with the BP control criteria; (10) the proportion of participants with ≥ 30% decrease in albuminuria from baseline to weeks 4, 8, 12, 24, 36, 48, 72, 96, 120, and 144 in accordance with the BP control criteria; and (11) the proportion of individuals with ≥ 50% decrease in eGFR from baseline to weeks 4, 8, 12, 24, 36, 48, 72, 96, 120, and 144 in accordance with the BP control criteria.

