### Statistics

In order to achieve a statistical power of 80%, the sample size assumed a non-inferiority margin of 18% (based on two-sided t test and a significance level of 0.025). This is based on the rate of change in proteinuria from baseline (Week 0) to week 24 of both losartan and fimasartan groups with a standard deviation of 62% [10, 12–14, 23]. Based on the assumption of a drop-out rate of 20%, a total of 468 patients are needed for randomization (with 234 patients per treatment arm).

The primary efficacy assessment finds that the fimasartan group is not inferior to the losartan group if the lower limit of a 95% two-sided confidence interval for the difference in the rate of change in proteinuria at week 24 between the fimasartan and losartan groups (control group - study group) is > − 18%. This is defined as the non-inferiority margin.

The major secondary efficacy assessment is determined by the incidence of combined cardiovascular and renal composite endpoints and is assessed using Kaplan–Meier curves, according with target BP at 144 weeks. The median survival time and confidence interval for the median survival time are presented. The log-rank test is used to compare the groups. Other secondary efficacy assessments are determined using the following methods. For continuous variables, descriptive statistics (number of individuals, mean, standard deviation, median, minimum, and maximum) for each time point are provided according to treatment group or the BP control criteria. The t-test is used to compare the inter-group difference in the rate of change. The inter-group difference in the amount of change is tested using the analysis of covariance, with the baseline values as covariates and the treatment groups as factors. The least squared mean and standard error are provided for each group. Frequencies and ratios are provided for categorical variables such as the proportion of individuals. For categorical variables, the Chi-square test, Fisher’s exact test, or Cochran–Mantel–Haenszel test is performed.

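### Other secondary endpoints (4) and (9): the tests named for the proportion with ACR below 300 mg/g leave out baseline ACR, which is valid but wastes power

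*Protocol article*

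**What the plan says.** Four statements in the protocol article bear on this point.

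- **Endpoint (4), drug comparison** (Other secondary endpoints): "the proportion of individuals who developed microalbuminuria (urine ACR < 300 mg/g) in the fimasartan and losartan groups at weeks 4, 8, 12, and 24".
- **Endpoint (9), BP-target comparison** (same section), followed to week 144: "the proportion of individuals with a change in microalbuminuria (urine ACR < 300 mg/g".
- **Entry at the baseline visit** (Table 1): "Urine protein: ACR ≥ 300 mg/g in spot urine". No upper limit is given.
- **Tests** (Statistics): "For categorical variables, the Chi-square test, Fisher’s exact test, or Cochran–Mantel–Haenszel test is performed". No covariate or stratum is named, and nothing says which of the three tests applies when.

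The same Statistics paragraph does use baseline for the amount of change, by analysis of covariance "with the baseline values as covariates and the treatment groups as factors". Randomisation is stratified by site only (Randomization section), so the design does not balance baseline ACR either.

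**The concern.** Success means falling below the value that every patient had to reach or exceed at entry. How far a patient must fall is therefore set by the starting value. A patient at 330 mg/g needs a fall of just over 9% (30/330). A patient at 3000 mg/g needs a fall of just over 90% (2700/3000). Baseline ACR is measured in everyone and is bound to be a strong predictor of this outcome.

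Chi-square and Fisher's exact tests cannot use it. CMH could, but only if baseline ACR is made the stratum. Leaving out so strong a predictor makes a true difference in responder proportions harder to detect. It also leaves the estimate in any one trial exposed to a chance imbalance in how many patients started just above 300 mg/g. At stake is the sensitivity of two other secondary endpoints. The primary interval and the analyses of continuous change are not touched.

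**Working it through.** **1. The plan's own sample size, to fix the number evaluable.** Inputs from Statistics: "In order to achieve a statistical power of 80%, the sample size assumed a non-inferiority margin of 18" (per cent), "with a standard deviation of 62" (per cent), 20% drop-out.

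n per arm = 2 × (1.960 + 0.842)² × 62² / 18² = 186.2, rounded up to 187. Then 187/0.80 = 233.75, so 234 per arm and 468 in total. This matches the article exactly. It does so with a one-sided 0.025 level and no true drug difference. The wording "based on two-sided t test and a significance level of 0.025", read literally, gives 226 evaluable and 283 randomised per arm. The simulations below use 187 evaluable per arm and test at two-sided 0.05.

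**2. Spread of change on the log scale.** If week-24/baseline ACR is lognormal with geometric mean g and log SD s, its SD is g × √[exp(s²) × (exp(s²) − 1)]. Setting this to 0.62 gives s = 0.59 at g = 0.8, 0.67 at g = 0.65 and 0.71 at g = 0.6. The values of g are assumptions.

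**3. How strongly baseline predicts success.** With g = 0.65 and s = 0.67, a control patient starting at b has P(ACR < 300) = Φ{[ln(300/b) − ln 0.65]/0.67}:

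- b = 330: Φ(0.50) = 69%
- b = 900: Φ(−1.00) = 16%
- b = 3000: Φ(−2.79) = 0.3%

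**4. Power at week 24, drug comparison.** Assumptions not in the documents: baseline ACR lognormal and truncated at 300 mg/g; control ratio 0.65; fimasartan/losartan ratio 0.75; log SD of change 0.67. The slope of week-24 on baseline log ACR is 1.0, 0.8 or 0.6, and values below 1 represent regression to the mean. There were 1,500 runs per row. The tests are uncorrected chi-square, logistic regression on log baseline ACR (likelihood ratio), and CMH on baseline-ACR quartiles.

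| Baseline median (log SD) | Slope | Chi-square | Logistic | CMH quartiles | Logistic gain (points) |
|---|---|---|---|---|---|
| 600 (0.7) | 1.0 | 76.7% | 85.5% | 85.1% | 8.9 |
| 600 (0.7) | 0.8 | 80.8% | 86.8% | 85.7% | 6.0 |
| 600 (0.7) | 0.6 | 86.7% | 90.3% | 89.3% | 3.6 |
| 900 (0.8) | 1.0 | 61.4% | 77.3% | 74.5% | 15.9 |
| 900 (0.8) | 0.8 | 69.1% | 79.6% | 77.7% | 10.5 |
| 900 (0.8) | 0.6 | 77.7% | 85.3% | 84.5% | 7.5 |
| 1300 (1.0) | 1.0 | 47.4% | 66.2% | 62.1% | 18.8 |
| 1300 (1.0) | 0.8 | 55.9% | 67.3% | 65.4% | 11.5 |
| 1300 (1.0) | 0.6 | 58.7% | 66.9% | 64.9% | 8.1 |

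Gains come from unrounded powers. The Monte Carlo standard error of a single power is at most √(0.25/1500) = 1.3 points.

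**5. Wider grid, slope 1.** With ratios 0.8 and 0.7 and log SD of change 0.5, 0.65 and 0.8, the logistic gain ran from 2.1 to 22.3 points. It was about 7 to 22 where chi-square power was below 80%, and about 2 to 12 where it was already above. A second set of runs at slope 1 had a control ratio of 0.7 and nine combinations of baseline spread and noise. It gave gains of 9 to 19 points at a difference of 0.3 log units (ratio 0.74) and 3 to 13 at 0.2 log units (ratio 0.82).

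**6. Type I error.** With no true difference (log SD of change 0.65, four baseline settings, 2,000 runs each), rejection rates for the three tests lay between 4.0% and 6.3%, with a standard error of about 0.5 point. The highest was for logistic regression in the setting with fewest responders.

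**7. CMH by site.** With patients assigned at random to 40 sites and no site effect, CMH stratified by site had power 3 to 6 points below chi-square in every row of the table. Site strata alone therefore do not recover the loss.

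**The case against.** The strongest reply is that the quoted sentence already lists CMH, a stratified test, and that the choice of strata is ordinary analysis-plan detail which a journal article may leave out. Much of that stands. A reader might infer that the plan commits these endpoints to crude two-by-two tests. It does not, and an unnamed stratum would not be a finding in itself. What remains is that the article names the tests, two of the three cannot use baseline ACR, and an analysis that followed the text to the letter could discard the strongest predictor although the same paragraph adjusts the amount of change for baseline.

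A second stronger reading is that chance imbalance at baseline would make the results biased or the tests invalid. The documents do not support this. Allocation is randomised, and the nominal error rate already covers such imbalance, as the null simulations show. Adjustment sharpens the estimate in the trial at hand; it does not repair an inflated error rate.

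Third, a reader might take 9 to 19 points as the established loss. That range needs a slope of 1 and a drug ratio of about 0.75. Entry on a spot ACR at or above a cut makes some regression to the mean likely, and the gain is then smaller. The sample size itself assumes no true difference between the drugs, so a ratio of 0.75 is a scenario and not the plan's expectation. This objection stands, and the range is widened accordingly.

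Finally, these are two of eleven other secondary endpoints with no power claim, and the amount of change in albuminuria is already analysed with baseline adjustment. That limits the importance of the point but does not remove it.

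**Conclusion.** The point holds as a minor, cost-free improvement. For endpoints (4) and (9), the named tests carry no baseline-ACR covariate or stratum although the endpoint cut equals the entry limit. The loss is of efficiency, not validity.

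For a week-24 drug comparison with 187 evaluable per arm, the loss is about 4 to 19 points of power at a treatment ratio of about 0.75, and about 2 to 22 points over the wider grid. It is smaller with regression to the mean, and in the second set of runs it was smaller at the smaller effect. Every scenario with a true difference showed a gain from adjustment. The baseline distribution, treatment ratio and slope are all assumed, and the log SD comes from the plan's 62% only through an assumed geometric mean.

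The figures should not be carried over to endpoint (9) at week 144. The reasoning about the cut applies there too, but that comparison has a different contrast, longer follow-up and unknown attrition, and it was not simulated.

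**What to change.** For endpoints (4) and (9), name one inferential analysis:

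- logistic regression of ACR < 300 mg/g on randomised group and log baseline ACR, reported as a standardised risk difference with its 95% confidence interval; or
- CMH stratified by prespecified baseline-ACR categories, not by site alone. In the table above, CMH on quartiles gained 2.6 to 14.7 points over chi-square, so most of the benefit is available within the tests already listed.

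Keep frequencies and crude proportions as description.

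The cost is a sentence or two of analysis wording and a few lines of code. No new data, patients or visits are needed. The article's Trial status section reports recruitment as ongoing, so on that status the choice could be fixed before the analysis.

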The safety analysis is based on adverse events, laboratory abnormalities, electrocardiography, chest X-rays, orthostatic hypotension assessments, and abnormal changes in body weight and pulse. Appropriate statistical analysis methods are used to compare groups with regard to differences in the rate of adverse events, abnormal laboratory values, or other parameters. Either the Chi-square test or Fisher’s exact test is used to assess differences in the incidence of adverse events between the groups. Continuous data, including laboratory values (hematology/blood chemistry, urinalysis) and vital signs (pulse rate, body weight, etc.), are presented in the form of descriptive statistics (mean, standard deviation, minimum, maximum, and median) by group and visit. Either a paired t-test or the Wilcoxon signed-rank test is used to test the intra-group difference in the continuous data between baseline and after drug administration. In addition, the two-sample t-test and Wilcoxon rank sum test is performed to test inter-group differences (in continuous variables) from baseline to after drug administration. Among all of the laboratory values, categorical data are divided into normal and abnormal results. The inter-group differences are tested using the Chi-square test or Fisher’s exact test. The McNemar’s test is used to compare differences in the categorical data between baseline and after drug administration.

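### Between-group changes in continuous safety variables are tested without baseline adjustment and, read literally, by two tests each: a minor, avoidable loss of precision

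*Protocol article*

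**What the plan says.** All the relevant text is in the Statistics section of the protocol article.

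- **Scope.** The safety paragraph covers laboratory values and vital signs: "Continuous data, including laboratory values (hematology/blood chemistry, urinalysis) and vital signs (pulse rate, body weight, etc.), are presented in the form of descriptive statistics".
- **Within-group tests.** "Either a paired t-test or the Wilcoxon signed-rank test is used to test the intra-group difference in the continuous data". The wording is a choice between two tests.
- **Between-group tests.** "the two-sample t-test and Wilcoxon rank sum test is performed to test inter-group differences (in continuous variables) from baseline to after drug administration". No covariate is named, and the two tests are joined by *and*.
- **Efficacy, for comparison.** For the other secondary endpoints, the between-group difference in amount of change is "tested using the analysis of covariance, with the baseline values as covariates and the treatment groups as factors".

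The article gives no standard deviation, correlation or power for any safety laboratory value. It attaches no significance level, margin or decision rule to these tests.

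**The concern.** The plan uses two methods for the same kind of quantity. A change from baseline in an efficacy variable is adjusted for baseline; a change from baseline in a safety variable is not. No reason is given, and the baseline safety values must exist, because the within-group tests compare them with later values.

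Two things follow. First, the change score generally leaves in variance that the baseline could remove, so a real difference between the drugs in a laboratory value is easier to miss. It also carries a chance baseline difference between the groups into that trial's estimate. Second, if both tests are run on every variable, each question has two p-values and nothing says which one counts.

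This is a stated method, not a detail left out of a condensed article, because the article names the tests.

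**Working it through.** **1. Patients available.** The article's sample size concerns proteinuria, but it gives a sensible number per drug. Inputs: margin 18%, SD 62%, power 80%, drop-out 20%, true difference 0, and 0.025 in one tail (which matches the two-sided 95% confidence interval rule).

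n = 2 × (1.960 + 0.842)² × 62² / 18² = 186.2, so 187 per drug; 187 / 0.80 = 233.75, so 234 per drug and 468 in total. This reproduces the stated figures. I use 187 evaluable patients per drug below. The figure has no other bearing on the safety tests.

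**2. Variance of the two analyses.** Let s0 and s1 be the SDs at baseline and follow-up, and r their correlation.

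- Change score: s0² + s1² − 2·r·s0·s1
- ANCOVA residual: s1²(1 − r²)
- Excess of the change score: (s0 − r·s1)²

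The excess is never negative and is zero when s0 = r·s1. With equal SDs (s0 = s1 = s) the variances become 2s²(1 − r) and s²(1 − r²). Their ratio, ANCOVA to change score, is (1 + r)/2, so the share removed is (1 − r)/2.

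**3. Size over a range of r (assumed, equal SDs).**

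| r | Change variance / s² | ANCOVA variance / s² | Share removed | Fall in standard error | Patients per drug with ANCOVA matching 187 on change | ANCOVA power where change has 80% |
|---|---|---|---|---|---|---|
| 0.4 | 1.20 | 0.84 | 30% | 16.3% | 131 | 92% |
| 0.6 | 0.80 | 0.64 | 20% | 10.6% | 150 | 88% |
| 0.8 | 0.40 | 0.36 | 10% | 5.1% | 168 | 84% |
| 0.9 | 0.20 | 0.19 | 5% | 2.5% | 178 | 82% |

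**4. Illustration.** Take potassium with an SD of 0.45 mmol/L and a true difference of 0.10 mmol/L. Both figures are assumptions; the article gives neither. Use 187 per drug, two-sided 0.05 and the normal approximation.

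- r = 0.4: change SD = 0.45 × √1.2 = 0.493, standard error = 0.493 × √(2/187) = 0.0510, z = 1.96, power 50%. ANCOVA SD = 0.45 × √0.84 = 0.412, standard error 0.0427, z = 2.34, power 65%.
- r = 0.6: 67% against 77%.
- r = 0.8: 92% against 95%.
- r = 0.9: both above 99%.

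**5. Two tests per variable.** In 5,000 simulated comparisons with no true difference and 187 per drug, each test alone rejected in about 5%. The rate at which at least one test gave p < 0.05 was 6.2% for normal data and 8.2% for lognormal data. The two tests disagreed in 2.0% and 6.4% of comparisons. A separate run of 20,000 replicates gave 6.1% for normal and 6.9% for skewed data. The inflation is therefore to about 6–8%, depending on skewness.

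**The case against.** The strongest reply is that nothing here is invalid and little depends on it. Under randomization the unadjusted comparison of change is unbiased and its tests hold their level. The safety tests carry no decision rule, and the mean-change comparison is not the only check: normal/abnormal laboratory results and adverse event incidence are also compared between groups. All of that stands, and it limits the point to precision in supportive analyses.

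Several stronger readings are tempting but not supported.

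- *A fixed saving of 15–30%.* This requires r between 0.7 and 0.4, which the article does not give. One range cannot cover all laboratory values; at r = 0.9 the saving is 5%.
- *The change score is always worse when r is below 1.* This holds under equal variances. In general the excess is (s0 − r·s1)², which can be zero with r below 1.
- *The potassium entry limits (3.5–5.5 mmol/L, Table 2) make the comparison biased.* The limits apply to all randomized groups alike and create no imbalance. For a given regression slope b the excess is s0²(1 − b)², so a narrower baseline spread reduces it.
- *Creatinine is left unprotected.* Change in eGFR between the drugs at weeks 4, 8, 12 and 24 is listed under Other secondary endpoints, and its amount of change is analysed by ANCOVA. Because eGFR is the creatinine-based MDRD estimate, the main renal comparison is already baseline-adjusted.
- *The noisier test favours the new drug in a non-inferiority trial.* The non-inferiority decision concerns proteinuria only. Allowing either of two tests to flag a difference would, if anything, raise more safety signals.

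The reading of *and* is also open. The other lists of alternative tests in the section use *or*, and the verb in this sentence is singular, so loose wording is quite possible. A rule for choosing between a parametric and a rank test may well sit in the analysis plan, which is not shown.

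**Conclusion.** The point holds as a minor one. The plan fixes an unadjusted comparison of change for continuous safety variables while adjusting for baseline in the equivalent efficacy comparison. The cost is precision, not validity. Under equal variances it is (1 − r)/2 of the variance, and its importance depends on how strongly each variable tracks within patients. Where tracking is weak (r near 0.4), the change score needs about 187/131 = 1.43 times as many patients for the same precision; at r = 0.9 the two methods are nearly equivalent. The two-p-value problem is real only if *and* is meant literally, and then it is modest: about 6–8% instead of 5% per variable. The figures rest on assumed correlations, equal variances at the two visits and, in the illustration, an assumed SD and difference. No stated conclusion of the trial depends on this, including non-inferiority on proteinuria.

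**What to change.** In the safety paragraph of the Statistics section, and in the analysis plan, replace the two between-group tests with one named analysis per variable: ANCOVA of the post-baseline value (or the change) on group, with the baseline value as covariate, as already specified for efficacy. State in advance which variables will be analysed on the log scale, or by a rank version with baseline rank as covariate, because of skewness. Report the adjusted between-group difference with its 95% confidence interval (a ratio where the log scale is used). If both existing tests are kept, say which one counts and change *and* to *or* if that is what is meant.

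The cost is a few lines of text and slightly different programming. No new data, visits or patients are needed. Trial status describes recruitment as ongoing, so on that description the change can be made before the data are analysed.
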